#### Demographic data

Demographic data is already available from questionnaires and a personal interview conducted as part of the Gutenberg Long Covid Study. The following will be evaluated for the immunoadsorption study:

- Age
- Gender
- Ethnic
- Smoking status
- Highest level of education
- Marital status
- Children
- Current occupation
- Occupation prior to SARS-CoV-2 infection

#### Clinical data

The clinical data is taken from the Gutenberg Long COVID Study, which was collected through questionnaires and personal interviews:

- Pre-existing conditions
- Time of SARS-COV-2 infection
- Vaccination status with regard to SARS-CoV-2
- Symptoms during SARS-COV-2 infection
- Hospitalization status during SARS-COV-2 infection
- Need for oxygen during SARS-CoV-2 infection

#### Laboratory tests and collection of biomaterial

During participation in the study, venous blood samples will be taken at various times by nursing staff or doctors trained in blood sampling. The parameters to be determined serve, on the one hand, to find or rule out alternative causes for the symptoms reported in the context of post-COVID syndrome and, on the other hand, to provide explanations for any improvements or worsening of symptoms during or after therapy. Most of the laboratory values for the individual participants are already available at the time of study inclusion from the examinations carried out during their participation in the Gutenberg Long COVID Study. Some parameters must be determined several times during study participation. Table 2 shows which parameters are determined at which point in the study.

In addition, a urine test is planned several times during the study, for which the subjects must provide at least 50 ml of midstream urine.

All analyses of blood and urine samples are performed in a pseudo-anonymous manner by the Central Laboratory of the University Medical Center Mainz.

Saliva samples for determining cortisol concentrations at different times of the day will be collected during an inpatient stay on the day before the first extracorporeal therapy of the respective cycle, as these must be processed promptly.

| Parameters | Time of collection | Material |
| --- | --- | --- |
| Complete blood count | E, vT1, nT1, vT2, nT2 | Serum |
| Sodium concentration | E, vT1, nT1, vT2, nT2 | Plasma |
| Potassium concentration | E, vT1, nT1, vT2, nT2 | Plasma |
| Calcium concentration | E, vT1, nT1, vT2, nT2 | Plasma |
| Phosphate concentration | E, vT1, nT1, vT2, nT2 | Plasma |
| Transferrin saturation | E, vT1, nT1, vT2, nT2 | Serum |
| Ferritin | E, vT1, nT1, vT2, nT2 | Serum |
| C-reactive protein | E, vT1, nT1, vT2, nT2 | Plasma |
| Antinuclear antibodies | E, vT1, nT1, vT2, nT2 | Serum |
| Daily profile of cortisol concentration in saliva | E, vT1, nT1, vT2, nT2 | Saliva |
| Thyroid-stimulating hormone | E, vT1, nT1, vT2, nT2 | Serum |
| 25-hydroxy vitamin D concentration | E | Serum |
| Vitamin B12 concentration | E | Serum |
| Immunoglobulin G concentration | E, vT1, nT1, vT2, nT2 | Serum |
| Antibodies against α-adrenoreceptors of subtypes 1-2 | E, vT1, nT1, vT2, nT2 | Serum |
| Antibodies against β-adrenergic receptors of subtypes 1-3 | E, vT1, nT1, vT2, nT2 | Serum |
| Antibodies against muscarinic acetylcholine receptors of subtypes M1-M4 | E, vT1, nT1, vT2, nT2 | Serum |
| Venous blood gas analysis | E, T1, T2 | Whole blood |
| Activated partial thromboplastin time (aPTT) | E, vT1, nT1, vT2, nT2 | Citrate plasma |
| International normalized ratio (INR) | E, vT1, nT1, vT2, nT2 | Citrate plasma |
| Fibrinogen concentration | E, vT1, nT1, vT2, nT2 | Citrate plasma |
| Albumin in spontaneous urine | E, vT1, nT1, vT2, nT2 | Midstream urine |
| Creatinine in spontaneous urine | E, vT1, nT1, vT2, nT2 | Midstream urine |
| Total protein in spontaneous urine | E, vT1, nT1, vT2, nT2 | Midstream urine |
| Urine sediment including acanthocyte concentration | E, vT1, nT1, vT2, nT2 | Midstream urine |
| Albumin/creatinine ratio in spontaneous urine | E, vT1, nT1, vT2, nT2 | Midstream urine |
| Total protein/creatinine ratio in spontaneous urine | E, vT1, nT1, vT2, nT2 | Midstream urine |

1 table: Overview of the parameters determined from the respective biomaterial and the time of material collection (E = evaluation tests; T1 = during therapy cycle 1; T2 = during therapy cycle 2; vT1 = before therapy cycle 1; nT1 = after therapy cycle 1; vT2 = before therapy cycle 2; nT2 = after therapy cycle 2).

### Medical-technical examinations

- - - 1. Physical examination, anthropometry, and vital signs

Each study participant undergoes a physical examination by a physician, which includes auscultation of the heart and lungs and a clinical examination of the abdomen. The height and weight of each participant are recorded and used to calculate their body mass index.

Vital signs are recorded by medically trained personnel using electronic devices. Resting blood pressure is determined oscillometrically using an upper arm cuff after 5 minutes of physical rest in a sitting position, heart rate is determined using pulse oximetry, body temperature is measured via tympanic measurement with a laser thermometer, and respiratory rate is counted.

The results of the physical examination, anthropometry, and vital signs are taken from the data of the Gutenberg Long COVID Study.

In addition to the measurements of vital signs, which are determined for the collection of study data, heart rate, oxygen saturation, and blood pressure are continuously monitored during each therapy session, both during the active and placebo therapy, or every ten minutes in the case of blood pressure, using electrical devices.

- - - 1. 12-channel ECG

A 12-channel ECG is recorded for each study participant as part of the Gutenberg Long COVID Study. Data from the findings of these 12-channel ECGs will be transferred to the immunoadsorption study, as this could provide clues to the causes of the symptoms experienced by the participants. The rhythm, QT time, ST segment findings, and any block patterns are transferred.

- - - 1. Spirometry

In order to record the lung function of the subjects and to determine the possible influence of the therapy cycles on lung function, as well as to evaluate a possible correlation between the reported dyspnea symptoms and the measured lung function, spirometry will be performed on each participant. Initially, each subject has already undergone spirometry, which was performed during participation in the Gutenberg Long COVID Study. After each therapy cycle, another spirometry test will be performed by the Center for Preventive Cardiology. Parameters for determining obstructive and restrictive ventilation disorders will be measured, as well as the diffusion capacity of the lungs.

- - - 1. Neurological examinations

To objectively assess neurological symptoms, neurological examinations will be performed on each study participant. The initial examination will take place when participants enroll in the Gutenberg Long COVID study. To determine the possible effects of the therapy on neurological symptoms, identical examinations will also be performed after each therapy cycle.

*Vibration sensitivity*

The vibration perception threshold is measured using a tuning fork on the metatarsophalangeal joint of the big toe as an indication of a possible sensory disorder.

*Force measurement*

Muscle strength is determined, for example, by measuring the pressure exerted by the hand muscles when squeezing a rubber balloon with the dominant hand. The force applied is measured using a vigorimeter.

*Smell test*

The smell test is performed using a test battery of standardized smell sticks containing eight different smells.

*Testing pain sensitivity*

Pain sensitivity is tested using a pinprick stimulator and the sensation of pressure pain is measured using a Wagner pressure pain algometer.

- - - 1. Neurocognitive testing

Various neurocognitive functions are tested using the Montreal Cognitive Assessment (MoCA). This is a ten-minute test with various tasks that can be scored with a total of up to 30 points. It tests abilities in the areas of memory, attention, verbal abstraction, visuospatial abilities, concentration, and language comprehension.

- - - 1. Post-COVID-19 Functional Status Scale (PCFS)

The PCFS is a self-assessment tool that helps to objectively measure and compare the severity of symptoms experienced by people with post-COVID. Patients are asked to describe their condition or fill out a questionnaire. Each condition is assigned a value. The greater the severity of the symptoms described by the condition, the higher the point value on a scale of 0-4. The PCFS has been validated on cohorts of post-COVID patients and is therefore particularly suitable for assessing symptom severity.

- - - 1. Assessment of the severity of fatigue symptoms

Three different questionnaires are used to objectively assess fatigue symptoms and the resulting limitations in everyday life. These are the Chalder Fatigue Scale, the Bell Score, and the Multidimensional Fatigue Inventory (MFI-20).

- - - - 1. *Chalder Fatigue Scale*

The Chalder Fatigue Scale is a set of 11 questions that assesses two dimensions of fatigue symptoms: physical performance and mental performance. Each question is answered using a 4-point Likert scale. It takes an average of 2-3 minutes to complete and can be repeated every 4 weeks. In the validation study, a sensitivity of 75.5% for chronic fatigue syndrome and a specificity of 74.5% were achieved.

The Chalder Fatigue Scale should be completed by each study participant as part of the evaluation examinations, before and after therapy cycle 1, before and after therapy cycle 2, and in the follow-up examination. It is completed digitally using a questionnaire on a tablet (iPad).

- - - - 1. *Bell Score*

The Bell Score is an assessment tool that can be used by both the patient and the examiner to measure the degree of limitation in daily life caused by fatigue symptoms. The limitation can be rated on a scale of 11, from 0 (bedridden) to 100 (no limitations, normal ability to perform all activities of daily living).

The Bell Score should be completed by each study participant as part of the evaluation examinations before and after therapy cycle 1, before and after therapy cycle 2, and in the follow-up examination. It is completed digitally using a questionnaire on a tablet (iPad).

- - - 1. Medical Research Council (MRC) Dyspnea Scale

In order to objectify the perceived dyspnea symptoms, make them more comparable, and be able to assess the possible effect of therapy on dyspnea symptoms, patients are asked about their symptoms using the MRC Dyspnea Scale, which uses 4 statements assigned a point value of 1-4 that describe situations in which dyspnea occurs. The subjects must then select the statement that best describes their situation.

- - - 1. Cranial MRI

All subjects are undergoing a cranial MRI at the Mainz Neuroimaging Institute as part of the Gutenberg Long COVID Study. The results will be used in the study " " to assess whether the patients' symptoms could have causes other than long COVID and whether patients with certain abnormalities respond particularly well or particularly poorly to therapy, as well as to investigate a possible correlation between the presence of autoantibodies and abnormalities in the MRI. T1, T2-TSE FLAIR, and rsfMRI will be measured on a Siemens Magnetron TRIO T3.

| Examination | Results from the Gutenberg Long Covid Study (evaluation) | Time |
| --- | --- | --- |
| Medical history interview and questionnaire | Yes | E |
| Anthropometry | Yes | E |
| Vital signs (HR, RR, temp., respiratory rate) | no | E, T1, T2 |
| 12-channel ECG | Yes | E |
| Spirometry | Yes | E, nT1, vT2, nT2, F |
| Neurological examination | Yes | E, nT1, vT2, nT2, F |
| Neurocognitive testing | Yes | E, nT1, vT2, nT2, F |
| PCFS score | No | E, nT1, vT2, nT2, F |
| Chalder fatigue scale | no | E, nT1, vT2, nT2, F |
| Bell score | No | E, nT1, vT2, nT2, F |
| MRC score | no | E, nT1, vT2, nT2, F |
| Blood sampling | yes | E, T1, nT1, T2, vT2, nT2, F |
| Urine analysis | Yes | E, nT1, vT2, nT2, F |
| Cranial MRI | yes | E |
| Psychological questionnaires | yes | E, nT1, vT2, nT2, F |

Table2 : Overview of examinations performed, proportion of examinations whose results can be used from the Gutenberg Long COVID study as part of the evaluation examinations, and when the respective examinations are performed. (E = evaluation examinations; T1 = during therapy cycle 1; T2 = during therapy cycle 2; vT1 = before therapy cycle 1; nT1 = after therapy cycle 1; vT2 = before therapy cycle 2; nT2 = after therapy cycle 2, F = follow-up; for most examinations, the evaluation examination is equivalent to the examination before therapy cycle 1).

- 1. Informing participants about examination results

After each examination, the test subjects will receive brief information if there are any relevant examination results. After completion of the study, participants will receive a detailed written report of the findings and an appointment will be offered to discuss the findings.

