## **6. Target parameters**

6.1 Primary endpoints:

Effectiveness of immunoadsorption on symptom burden in patients with post-COVID syndrome measured by the values of:

- Post-COVID-19 functional status scale (PCFS)
- Chalder Fatigue Scale
- Montreal Cognitive Assessment (MOCA)
- MFI-20
- Bell Score
- Strength measurement

and comparison before and after active treatment and before and after sham treatment (before treatment cycle 1/after treatment cycle 1 and before treatment cycle 2/after treatment cycle 2).

6.2 Secondary endpoints:

- Frequency of adverse events under active and sham treatment
- Prevalence of anti-adrenergic and anti-muscarinic autoantibodies in patients with post-COVID syndrome:
  - Proportion of subjects with evidence of anti-α1-adrenoreceptor Abs
  - Proportion of subjects with evidence of anti-α2-adrenergic receptor Abs
  - Proportion of subjects with evidence of anti-β1-adrenoreceptor Abs
  - Proportion of subjects with evidence of anti-β2-adrenergic receptor Abs
  - Proportion of subjects with evidence of anti-β3-adrenoreceptor Abs
  - Proportion of subjects with evidence of anti-M1 acetylcholine receptor Abs
  - Proportion of subjects with evidence of anti-M2 acetylcholine receptor Abs
  - Proportion of subjects with evidence of anti-M3 acetylcholine receptor Abs
  - Proportion of subjects with evidence of anti-M4 acetylcholine receptor Abs
- Concentration of:
  - Anti-α1-adrenoreceptor Abs
  - Anti-α2-adrenoreceptor Abs
  - Anti-β1-adrenoreceptor Abs
  - Anti-β1 adrenoreceptor Abs
  - Anti-β1 adrenoreceptor Abs
  - Anti-M1 acetylcholine receptor Abs
  - Anti-M2 acetylcholine receptor Abs
  - Anti-M3 acetylcholine receptor Abs
  - Anti-M4 acetylcholine receptor Abs

Before and after active and sham treatment (before therapy cycle 1/after therapy cycle 1 and before therapy cycle 2/after therapy cycle 2).

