## **Study design**

The Mainz immunoadsorption study in adults with post-COVID is a single-center, randomized, controlled, single-blind study with a cross-over design that aims to investigate the potential effect of immunoadsorption therapy on symptom burden in people with post-COVID. The study is being conducted by an interdisciplinary team of investigators.

Included subjects are first randomized to receive either 5 verum treatments (immunoadsorption with TR-350 adsorber) or 5 sham treatments (connection to the Plasauto Sigma without adsorber). All subjects will receive both the real treatment and the sham treatment unless they decide against the respective therapy cycle before the start of the respective therapy cycle. Randomization is only used to determine which treatment is given first.

Participating subjects may withdraw from the study at any time, including after the first therapy cycle or before the second therapy cycle.

The subjects are blinded because they do not know whether the treatment is being carried out with or without an adsorber, and it is also not apparent to the subjects, as the TR-350 adsorber and Plasauto Sigma are set up behind a curtain that is not visible to the patient and remain there throughout the treatment.

The blinding of the subjects serves to assess the actual effect of the therapy without the influence of the therapy arm on the patients' reports. Since the therapeutic effects in the present study are predominantly measured using self-report instruments, such an approach seems essential to minimize the influence of distortions caused by psychological effects of the verum therapy on the study results.

[figure not shown]

1 Figure Study design and flow chart

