**Ammendments to the Mainz immune adsorption study in adults with post-COVID (IAMPOCO)**

1. Study participants do not necessarily have to have participated in the Gutenberg Post-COVID Study prior to participating in the study, but may also be included if comparable examinations and assessments have been carried out by post-COVID outpatient clinics or post-COVID specialist practices.

2. The only neurological examinations carried out as part of the study are pain assessment using a numerical analog scale and cognitive assessment using the MocA.

3. Anticoagulation for both immune adsorption and sham treatment is achieved using citrate anticoagulation and continuous heparin administration at 1000iE/h.

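### MoCA is scheduled five times with no provision for alternate versions, so a practice gain would count as improvement in the before/after primary endpoint and use up headroom, although it does not bias verum minus sham

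*Protocol*

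**What the plan says.** - Section 6.1 lists the MoCA among six primary measures and defines the endpoint as the "comparison before and after active treatment and before and after sham treatment". It names no verum-minus-sham contrast.
- The neurocognitive testing paragraph describes a task-based test scored up to 30 points: "It tests abilities in the areas of memory, attention, verbal abstraction, visuospatial abilities, concentration, and language comprehension".
- Table 2 gives the schedule: "Neurocognitive testing | Yes | E, nT1, vT2, nT2, F". Its legend adds that "for most examinations, the evaluation examination is equivalent to the examination before therapy cycle 1", and the Yes means that the first value may be taken over from the cohort study. Amendment 1 also admits participants assessed at outside post-COVID clinics or practices.
- The neurological examinations paragraph states that "identical examinations will also be performed after each therapy cycle". The MoCA has its own heading further down, but Amendment 2 reads: "The only neurological examinations carried out as part of the study are pain assessment using a numerical analog scale and cognitive assessment using the MocA".
- The Study design section describes a sham-controlled cross-over. On allocation it says: "Randomization is only used to determine which treatment is given first".
- Section 9.6 puts a treatment cycle at one week.
- The Biometrics section sizes the trial on the MoCA: median 27, interquartile range 25 to 28, a 2-point difference, and a one-sided two-group Wilcoxon-Mann-Whitney test.

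No section says which MoCA version is used at any visit or mentions practice effects.

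**The concern.** Someone who has recently met a set of memory and attention tasks may do better on them the second time without any change in health. Two consequences follow if the same version is reused.

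First, an endpoint worded as change from before to after, within each treatment, cannot tell practice from benefit. An apparent MoCA improvement under verum could be wholly practice.

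Second, the scale has little room at the top. In the cohort that the protocol cites, the median lies 30 − 27 = 3 points below the cap and the upper quartile 30 − 28 = 2 points below it. Points gained by practice are no longer available to show a treatment effect. Unlike the first problem, this one cannot be fully repaired in the analysis, because the test version is fixed when the visit takes place.

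**Working it through.** **1. The plan's own figure.** With the usual efficiency factor 3/π for the Wilcoxon-Mann-Whitney test, d = 1.0, n = 19 per group and one-sided alpha 0.05:

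- noncentrality = 1.0 × √(19 × (3/π) / 2) = 3.01
- degrees of freedom = 2 × 19 × 3/π − 2 = 34.3
- power = 0.904

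The stated 19 per group for 90% power is reproduced, and this point does not affect it.

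**2. Does the text imply the same test?** The sentence on identical re-examination stands in the neurological block. Amendment 2 keeps two neurological examinations and names the MoCA as one, so in the amended protocol the sentence reaches the MoCA. It says that the examination is identical. It does not say that words and items are reused, and no passage says that they are varied.

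**3. Within-treatment change.** The documents give no practice gain, so the gains are assumptions: g1 points in cycle 1 and g2 in cycle 2, with zero treatment effect. With 20 participants per sequence, each treatment has 40 change scores, half from each cycle.

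- Mean change under either treatment: m = (g1 + g2)/2
- Noncentrality of the one-sided one-sample t-test: m × √40 / SD
- SD of change: also assumed, from 1.5 to 2.22. The upper value is the cross-sectional SD implied by the interquartile range, (28 − 25)/1.349 = 2.22.

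Examples: 0.375 × 6.32 / 2.22 = 1.07 and 0.75 × 6.32 / 1.5 = 3.16. Simulated rejection rates under verum, with 20,000 trials per setting:

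| g1, g2 | m | SD 1.5 | SD 2.0 | SD 2.22 |
|---|---|---|---|---|
| 0, 0 | 0 | 0.050 | 0.050 | 0.053 |
| 0.5, 0.25 | 0.375 | 0.464 | 0.314 | 0.278 |
| 1.0, 0.5 | 0.75 | 0.927 | 0.749 | 0.677 |

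The rates under sham are practically the same.

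**4. Verum minus sham.** In the same simulations the cross-over contrast, allowing for period, rejects in 0.048 to 0.055 of trials, with a mean difference of about 0. A first-period comparison of the two groups behaves likewise (0.048 to 0.053). The gain is common to both treatments and randomized order balances it.

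**5. Headroom.** Take scores as normal around 27 with SD 2.22, rounded and capped at 30, and add a true 2-point gain. The visible difference is:

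| Practice gain already present | Visible part of a 2-point gain |
|---|---|
| 0 | 1.62 |
| 0.5 | 1.49 |
| 1.0 | 1.34 |

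In a first-period comparison of change scores (19 per group, one-sided Mann-Whitney, true effect 2), 1 point of practice lowers power from about 0.96 to 0.85 with an SD of change of 1.5, and from about 0.74 to 0.62 with 2.22. These powers shift by up to about two percentage points with the handling of rounding. If only the after-scores are compared, the loss is about 1 to 2 percentage points.

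**The case against.** The strongest reply is that the design already deals with practice. A gain seen under both treatments is exactly what a sham arm and randomized order remove, and the sample size rests on a two-group comparison. This stands: step 4 shows no bias between treatments. A reader might infer that practice could make verum look better than sham, but the documents do not support that.

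Three further readings also go too far:

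- **That the protocol prescribes the same items.** It does not. Repeating an examination is compatible with changing the version, and a test manual may settle this. The literal reading comes from the neurological text, Amendment 2 and silence on versions taken together.
- **That withdrawal before cycle 2 leaves a material imbalance.** Take 18 completers in the verum-first sequence and 14 in the sham-first sequence, with raw means pooled. With g1 = 1 and g2 = 0 the bias is 20/34 − 20/38 = 0.06 points. With g2 = 0.5 it is 27/34 − 29/38 = 0.03 points. This is negligible.
- **That an assumed gain can be expressed as a share of the 2-point difference.** That difference belongs to a two-group comparison, to which shared practice contributes about nothing. The Biometrics section also words it as a reduction in score, which needs separate reconciliation.

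It is also fair that this concerns one of six measures. The four questionnaires and the strength measurement have no memory items to learn. A statistical analysis plan may define the treatment contrast. It could not restore lost headroom or change which version was administered.

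**Conclusion.** The point holds in limited form, as a cheap improvement. The protocol schedules five MoCA administrations, provides for no alternate versions, and words the primary endpoint so that a practice gain counts as improvement under both treatments. If the within-treatment changes were tested as worded, gains averaging 0.375 to 0.75 points per cycle would produce false positives in about 28% to 93% of trials, against a nominal 5%.

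Between treatments the risk runs the other way. One point of practice shrinks the visible part of a true 2-point gain from about 1.6 to 1.3 points, so a real effect may be missed.

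These sizes rest on assumed gains, on assumed SDs of change and on a normal approximation to the quoted median and quartiles. That the same version is repeated is the literal reading, not an explicit statement. If alternate versions are already intended, one sentence would settle that part.

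**What to change.** - In the neurocognitive testing paragraph and in Table 2, state that alternate MoCA versions are used at the trial's own visits: nT1, vT2, nT2, F, and vT1 if the test is given there. Balance the order of versions across participants, independently of treatment sequence, and repeat no version within a cycle.
- Where the E value comes from the cohort study or an outside clinic, the trial cannot assign its version. Record which version was used and give a different one at nT1.
- Read the MoCA result as the verum-minus-sham difference in change, with a period term, and not as the change within a treatment alone. This complements the version schedule and does not replace it.

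The cost is a sentence in the protocol, a version schedule for the site and one recorded item for the version at E. No visit is added. The downside is small differences in difficulty between versions, which the balanced order averages out over the trial's own visits.

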The possible pathomechanisms suspected to be behind these syndromes are diverse. However, the pathogenesis and underlying causes are not yet fully understood.^6^ Similarly, the causes of post-COVID syndrome are still unclear.^4^ Both clinical pictures are thought to involve autoimmune mechanisms triggered by the body's response to infection and sustained by the similarity of the body's own proteins to pathogen components (molecular mimicry).^7In^the context of this autoimmunity, antibodies against the body's own structures may also be formed, such as antinuclear antibodies, which target components of the cell nucleus.^7^ In patients suffering from ME/CFS, antibodies against α- and β-adrenergic receptors and against muscarinic acetylcholine receptors, among others, have been detected.^8^ No correlations between antibody concentrations and the severity of the disease or the clinical picture of ME/CFS could be demonstrated, nor are these antibodies specific or sensitive for ME/CFS.^8, 9^

With the detection of autoantibodies in patients with ME/CFS, forms of therapy that specifically target the formation of autoantibodies have also been investigated. For example, two randomized controlled trials involving 30 and 151 ME/CFS patients investigated B-cell-depleting therapy with the anti-CD-19 antibody rituximab versus placebo. The results showed no significant improvement in fatigue symptoms compared to placebo, although a reduction in B-cell concentration was achieved.^10, 11^ In the primary endpoints (improvement in fatigue symptoms after 3 months and after 24 months), there was no significant difference between placebo and rituximab therapy in either study.^10, 11^

Immunoadsorption is another therapeutic option for reducing the concentration of autoantibodies. In this procedure, the patient's blood is first separated into cellular components and plasma, and then the plasma is passed through adsorbents.^12^ The adsorbents have specific surfaces for binding different classes of immunoglobulins, so that the plasma is then largely purified of immunoglobulins and thus also of autoantibodies and returned to the patient together with the cellular components.^12^ This reduces the concentration of immunoglobulins and thus also the concentration of autoantibodies. ^12, 13^ Immunoadsorption is one of the established treatment options for many antibody-mediated autoimmune diseases.^14^

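### The rule on telling participants relevant results after each examination does not exclude post-cycle IgG and autoantibody results, which could reveal allocation before later self-reports

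*Protocol*

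**What the plan says.** Three parts of the protocol bear on this.

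- **Disclosure.** The item on informing participants about examination results, after Table 2, has two stages. During the study: "After each examination, the test subjects will receive brief information if there are any relevant examination results". Afterwards: "After completion of the study, participants will receive a detailed written report of the findings". The first stage names no test, gives no definition of relevance and makes no exception.
- **Measurements.** Table 2 counts blood sampling among the examinations: "Blood sampling | yes | E, T1, nT1, T2, vT2, nT2, F". Table 1 places the treatment-sensitive markers before and after both cycles, for example "Immunoglobulin G concentration | E, vT1, nT1, vT2, nT2 | Serum" and "Antibodies against β-adrenergic receptors of subtypes 1-3 | E, vT1, nT1, vT2, nT2". The α-adrenergic and muscarinic antibodies follow the same schedule. On the effect of adsorption, the scientific background says: "This reduces the concentration of immunoglobulins and thus also the concentration of autoantibodies".
- **Blinding.** The study design section treats participant blinding as essential because "the therapeutic effects in the present study are predominantly measured using self-report instruments". It describes a curtain hiding the equipment. Section 9.5 uses the same device, tube system and flows for both treatments, and amendment 3 sets the same anticoagulation for both.

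**The concern.** The protocol relies on participants not knowing which treatment they have had, yet it gives them results during the study with no exclusion for the markers that the treatment is meant to change. A marked fall in IgG after a cycle points to verum. The design has two treatments, and randomization fixes only their order, so knowing one cycle gives away the other.

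Four of the six primary endpoints are questionnaires on function or fatigue (PCFS, Chalder, MFI-20 and Bell). A participant who believes that the coming cycle is sham may rate it accordingly. Later analysis cannot restore a blind lost in this way.

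**Working it through.** The plan gives no figure on this point, and its sample size calculation does not bear on it. The check sets the passages side by side.

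1. **Does the rule reach these results?** It applies after each examination. Blood sampling is listed as an examination at nT1 and nT2 (after cycles 1 and 2). IgG and 2 α + 3 β + 4 muscarinic = 9 receptor antibodies are scheduled at those points. Nothing in the protocol removes them from the rule. Whether a low value counts as relevant is left to whoever applies it.

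2. **Would a result be informative?** By the protocol's account adsorption lowers immunoglobulins and autoantibodies. Sham is the same circuit without the adsorber. A marked post-cycle fall therefore suggests verum.

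3. **Do the blinding measures cover it?** The curtain, device, tubing, flows and anticoagulation address what the participant sees and feels during a session. None concerns laboratory results.

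4. **Who is exposed, and when?** With 40 participants randomized 1:1, 20 start with verum. Table 2 schedules PCFS, Chalder and Bell at E, nT1, vT2, nT2 and F, with E standing in for vT1.

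| Sequence | First sample with a treatment-related fall | Self-reports still to come |
| --- | --- | --- |
| Verum first (20) | nT1 | vT2, nT2, F |
| Sham first (20) | nT2 | F at most |

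This takes the nT1 and nT2 questionnaires as completed before the results of the same time point are known. The protocol does not state assay turnaround. The note to Table 4 says before-and-after samples are drawn during the extracorporeal sessions, which does not settle the order.

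5. **What does this mean for the primary comparison?** That comparison uses the change across each cycle. There are 40 × 2 = 80 participant-cycles. On the ordering in step 4, only the sham cycle of verum-first participants is exposed: at most 20 of 80 participant-cycles, or 20 of the 40 sham cycles.

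6. **Size, as an assumption only.** Suppose a share p of verum-first participants is told, and the knowledge shifts their change over cycle 2 by δ standard deviations. The mean sham change over all 40 then moves by (20/40) × p × δ. With p = 1, δ = 0.2, 0.3 and 0.5 give 0.10, 0.15 and 0.25 SD. If vT2 and nT2 scores shift equally, δ is 0 and the change score is unaffected. Neither p nor δ is in the documents, so no error rate follows from this.

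**The case against.** The strongest reply is that the protocol never says IgG or autoantibody values are given to participants. The in-study information is brief and conditional, and the detailed report waits until the study is complete. The laboratory section says the tests serve partly to find other causes of the symptoms, and section 10.1 offers advice if a disease is diagnosed. Read together, relevant results may mean incidental diagnoses and not the expected effect of treatment. This stands as a plausible reading, and it rules out any claim that allocation is disclosed by design. It does not close the gap, because the text does not confine the rule to that reading.

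A reader might infer more than the documents support:

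- *That the curtain is the only protection.* It is not: device, tubing, flows and anticoagulation are also matched.
- *That one result breaks the blind for both periods.* It would reveal both allocations, but nT1 questionnaires may already be recorded, and a treatment-related fall after cycle 1 arises only in verum-first participants.
- *That the bias favours verum, or that informed participants leave before cycle 2.* Both are plausible. The study design section does allow a participant to decline the second cycle. Nothing in the protocol shows either effect or its size.

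**Conclusion.** The point holds in a limited form. The disclosure rule as written leaves open a route to unblinding that no other passage closes, and this sits badly with the protocol's own reason for blinding participants. It is a permission that needs narrowing, not a stated disclosure of allocation.

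The main exposure is in verum-first participants told of a low value after cycle 1, affecting self-reports at vT2, nT2 and F. This rests on three assumptions: that someone judges such a value relevant, that the result is available before those assessments, and that the participant understands what it implies. The documents do not allow the size or direction of any bias to be derived. The change is worthwhile because it is cheap and protects the outcomes on which the trial mainly relies.

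**What to change.** Amend the item on informing participants about examination results. State that IgG, receptor autoantibody and other results expected to change with adsorption are not given to participants until their last self-report assessment at follow-up, except where a result needs medical action. They are then supplied in the written report already planned after completion. The patient information should say the same.

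The cost is a short change to the text and a wait for non-urgent laboratory results. Asking each participant after each cycle which treatment they think they received is an optional addition: it would help to judge how well the blind held, but it does not close the gap. Withholding the results from staff who administer outcome scales is likewise a matter of preference in a trial declared single-blind.
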